### Data Management

Clinical and demographic data are recorded on standardized case report forms (CRFs) and tracked via study identification codes. To ensure data integrity, a designated investigator conducts weekly quality assurance reviews to verify completeness and internal consistency. Signed informed consent documents are stored in secure, restricted-access files separate from the CRFs. The final dataset undergoes a comprehensive validation review by a senior investigator prior to statistical analysis.

### Ethical Considerations

The Ethics Review Committee of Peking Union Medical College Hospital, Chinese Academy of Medical Sciences, approved the study (approval number I-24PJ0689), which complies with the Declaration of Helsinki, and was registered on the Chinese Clinical Trial Registry (identifier ChiCTR2400083246; registered April 2024). Before enrollment, investigators will explain potential benefits and risks, and participants will provide written informed consent. Participant confidentiality will be protected throughout the study by restricting data access to authorized investigators. Treatment-emergent adverse events will be managed at no cost to participants at the study institution. Study findings will be presented at scientific conferences and submitted to peer-reviewed journals. Authorship will follow International Committee of Medical Journal Editors (ICMJE) criteria, and the manuscript will be written and revised by the authors; no professional writers will be used. The protocol is registered with the Chinese Clinical Trial Registry, and the participant-level dataset will be available from the corresponding author upon reasonable request.

## Results

The study was funded by the National Natural Science Foundation of China (T2341003) in 2023. Recruitment officially commenced on May 24, 2024. As of submission, the study is ongoing, with data collection expected to be completed by December 2027.

## Discussion

### Principal Findings

This protocol describes a multistage research program designed to develop, evaluate, and optimize an AI-enabled IMT intervention for common mental disorders. We hypothesize that IMT, by tailoring musical stimuli to patient-specific preferences through generative AI, will yield superior response rates compared with nonindividualized receptive music therapy, and that these therapeutic effects will be accompanied by measurable changes in quantitative EEG characteristics. The sequential study design enables iterative refinement: study 1 establishes neurophysiological benchmarks, study 2 provides preliminary efficacy data for the nonindividualized protocol, study 3 directly compares the 2 approaches in an RCT, and study 4 validates a prediction model to identify patients most likely to benefit from IMT.

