Study 4 (Prediction Validation)	A prospective cohort study (n=60) in which all participants receive IMT, and the prespecified prediction model derived from studies 1‐3 is applied at baseline to classify participants as predicted responders or nonresponders.	Validates the prediction model in an independent sample. Unlike study 2, which evaluates the nonindividualized intervention, study 4 exclusively administers IMT and focuses on predictive accuracy rather than treatment efficacy.

a MDD: major depressive disorder.

b GAD: generalized anxiety disorder.

c PI: primary insomnia.

d HC: healthy control.

e EEG: electroencephalography.

f RCT: randomized clinical trial.

g IMT: individualized (receptive) music therapy.

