**Figure 1. F1:**
[figure not shown]
Study flowchart. MDD: major depressive disorder; GAD: generalized anxiety disorder; PI: primary insomnia; non-indiv: nonindividualized; EEG: electroencephalography.

The 4 studies are designed as a sequential translational pipeline in which each stage builds upon the preceding one. Study 1 serves as an exploratory pilot to calibrate clinical and EEG assessment procedures, verify protocol feasibility, and generate preliminary hypotheses regarding disorder-specific neurophysiological features. Although the sample size (n=20) is insufficient for definitive biomarker identification, this study provides essential groundwork for refining the measurement framework used in subsequent stages. Study 2 then evaluates the efficacy and safety of nonindividualized receptive music therapy in a larger cohort, establishing the clinical and neurophysiological benchmarks against which the individualized intervention will be compared. Study 3 directly compares the 2 approaches in a randomized controlled framework, enabling assessment of the incremental benefit of AI-enabled personalization. Finally, study 4 validates a treatment-response prediction model developed from the cumulative data of studies 1 through 3; this study is distinct from study 2 in that all participants receive IMT and the primary objective is to evaluate predictive accuracy rather than treatment efficacy per se.

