### Treatment-Response Prediction Model

The treatment-response prediction model to be validated in study 4 will be developed using data from studies 1 through 3. Candidate predictors will include baseline demographic characteristics (age, sex, and education), clinical variables (baseline symptom severity scores, disorder diagnosis, duration of illness, and medication status), music preference profiles (STOMP-R scores), and baseline neurophysiological features (resting-state EEG spectral power and frontal alpha asymmetry). The outcome variable for model development will be treatment response at 8 weeks, defined as a reduction of 50% or greater in the disorder-specific primary outcome measure. Model development will use logistic regression with regularization (elastic net) to handle the potentially large number of candidate predictors relative to the sample size, with internal validation using 10-fold cross-validation. The final model will be prespecified and locked before its application to the study 4 validation cohort. Model performance in study 4 will be assessed using discrimination metrics (area under the receiver operating characteristic curve, sensitivity, and specificity) and calibration measures (Hosmer–Lemeshow test and calibration plots). Should the cumulative sample from studies 1 through 3 prove insufficient for robust model development, alternative approaches such as penalized regression or decision-tree methods will be considered, and the model validation in study 4 will be framed accordingly. A detailed statistical analysis plan for the prediction model will be finalized before study 4 enrollment commences.

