
### Future Directions

If the pilot RCT demonstrates promising results, a fully powered, multicenter definitive trial will be warranted to confirm the efficacy of IMT across diverse clinical populations. To disentangle the personalization effect from the additional attention and engagement inherent in the IMT procedure, the definitive trial should consider a 3-arm design that adds an attention-matched sham-personalization control (in which participants complete weekly preference ratings but receive nonindividualized music), enabling the specific contribution of stimulus personalization to be isolated. Future studies should also incorporate longer follow-up periods (eg, 12 to 24 wk) to assess the durability of therapeutic effects and the potential for relapse prevention. Adequately powered, diagnosis-stratified samples will be required to draw firm disorder-specific conclusions for MDD, GAD, and PI, and to support confirmatory neurophysiological inference. The prediction model developed in study 4, if validated, could serve as a clinical decision-support tool for identifying patients most likely to benefit from individualized interventions; further refinement using machine-learning approaches with larger datasets would enhance its generalizability. Additionally, the integration of multimodal neuroimaging (combining EEG with fMRI or fNIRS) in future protocols could provide a more comprehensive understanding of the neural circuits engaged by IMT. Finally, investigating the applicability of the IMT framework to other psychiatric conditions, as well as to pediatric and geriatric populations, represents an important direction for extending the reach of this approach.

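### Study 4 can show who responds while receiving IMT, but not who benefits from IMT, as the Discussion claims

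*Protocol article*

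**What the plan says.** Under Principal Findings, the protocol article says that "study 4 validates a prediction model to identify patients most likely to benefit from IMT". Under Future Directions it says that the model, if validated, "could serve as a clinical decision-support tool for identifying patients most likely to benefit from individualized interventions".

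The Methods describe something narrower. Table 1 in Study Design defines study 4 as "A prospective cohort study (n=60) in which all participants receive IMT", with the locked model applied at baseline to "classify participants as predicted responders or nonresponders". The text after Figure 1 says that "the primary objective is to evaluate predictive accuracy rather than treatment efficacy per se".

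The section Treatment-Response Prediction Model says that the model "will be developed using data from studies 1 through 3". Its outcome is a fall of at least 50% in the disorder-specific score at 8 weeks. The candidates are all baseline variables: demographics, resting-state EEG features, and a middle group that reads "clinical variables (baseline symptom severity scores, disorder diagnosis, duration of illness, and medication status), music preference profiles (STOMP-R scores". Neither treatment arm nor an arm-by-predictor term is listed. For validation, "Model performance in study 4 will be assessed using discrimination metrics" (AUC, sensitivity, specificity) together with the Hosmer–Lemeshow test and calibration plots. No pass threshold is given, and a separate analysis plan for the model is to be finalized before study 4 enrolls.

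**The concern.** Benefit from IMT is a contrast: a patient's outcome with IMT against the outcome without it. Study 4 observes only the first half. A score that marks patients who would improve under either form of music therapy, for instance through baseline severity or illness duration, discriminates and calibrates just as well as one that marks patients who gain from individualization.

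The benefit wording matters because Future Directions attaches a use to it, namely selecting patients for individualized therapy. The protocol recognizes the principle elsewhere: Strengths and Limitations says that study 2 cannot attribute improvement to its intervention because it has no control group. Study 4 has none either, but the caution is not repeated there.

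**Working it through.** The protocol gives no power, precision or threshold for study 4 beyond n=60, so there is no figure to reproduce. The check is whether any study 4 result can bear on the Discussion's claim.

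**1. Same study 4 data, different benefit.** Suppose the model splits patients into equal halves and response under IMT is 84% in predicted responders and 57% in predicted nonresponders (illustrative values from step 3).

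- Sensitivity = 0.84/(0.84 + 0.57) = 0.60.
- Specificity = 0.43/(0.16 + 0.43) = 0.73.

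Now vary the unobserved response under nonindividualized therapy, using the protocol's 20-point threshold for clinical importance (Sample Size Calculation):

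| Response without IMT (predicted responders / nonresponders) | Gain from IMT | Sensitivity, specificity in study 4 |
|---|---|---|
| 84% / 57% | 0 / 0 points | 0.60, 0.73 |
| 64% / 57% | 20 / 0 points | 0.60, 0.73 |
| 84% / 37% | 0 / 20 points | 0.60, 0.73 |

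AUC and calibration are unchanged too, since they use the same scores and outcomes. This holds at any threshold.

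**2. Development data.** Study 1 is cross-sectional. Study 2 supplies at most 80 − 20 healthy controls = 60 patients, all on nonindividualized therapy. Study 3 supplies 300 randomized 1:1, so 150 per arm. That makes 360 outcomes: 150 under IMT and 60 + 150 = 210 under nonindividualized therapy. Pooled without an arm term, as the list stands, the model is mainly prognostic.

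**3. Illustration with zero benefit.** Simulation with 1,500 runs per setting: 360 development patients, 10 baseline predictors of which 4 are prognostic, ridge logistic regression standing in for elastic net, 60 validation patients on IMT, 70% response, and an IMT effect of exactly 0 for everyone. Prognostic strength (SD of the linear predictor) is an assumption.

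| SD | Mean AUC | Response, predicted responders / nonresponders | Lower 95% AUC limit above 0.5 |
|---|---|---|---|
| 0.5 | 0.61 | 77% / 64% | 34% |
| 1.0 | 0.73 | 84% / 57% | 85% |
| 1.5 | 0.80 | 88% / 52% | 99% |

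The last column uses a criterion that is not in the protocol. It shows only that respectable performance can coexist with no benefit.

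**4. Who gains most depends on the scale.** Take 80% and 60% response without IMT (average 70%) and 90% on average with IMT.

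- Constant odds ratio of about 4.0: odds 4 × 4.0 = 16, so 94%; odds 1.5 × 4.0 = 6, so 86%. Gains are about 14 and 26 points.
- Constant risk difference of 20 points: 100% and 80%. Gains are 20 and 20 points.

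The split, the 90% and the scale are all assumptions.

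**5. What study 3 could offer.** Only study 3 observes both treatments under randomization. With a median split of the score and no dropout there are 300/4 = 75 patients per arm-by-class cell. The contrast between classes in the arm difference has SE = √[4p(1 − p)/75].

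- p = 0.7: √(0.84/75) = 0.106; 95% half-width 1.96 × 0.106 = 20.7 points.
- p = 0.5: √(1.00/75) = 0.115; 95% half-width 22.6 points.

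**The case against.** The strongest reply is that this is wording, not analysis. The Abstract, Table 1 and the model section all speak of response and predictive accuracy. For that aim, discrimination and calibration in patients on IMT are the right measures. Future Directions is conditional and calls for further refinement. Whether IMT adds anything on average is tested in study 3, and the study 4 result would be read beside it. An arm-by-score analysis could also appear in the prediction-model analysis plan still to come, and the candidate list need not be exhaustive.

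Much of this stands. Study 4's analysis suits its stated objective, and the absence of an arm-by-score analysis from the article is not in itself a fault. What does not fall away is the claim. Principal Findings frames IMT's value as superiority over nonindividualized therapy, so benefit there naturally reads as a comparative gain. The average effect in study 3 does not show which patients gain. A later plan can narrow the claim or use study 3, but it cannot recover a comparator from a cohort in which everyone receives IMT. Adding arm terms during development would not change that, because study 4 could not test them.

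Two stronger readings are tempting and are not supported. A reader might infer that a worthless model would be declared validated at some known rate. The protocol sets no threshold, so such a rate belongs to whoever chooses one. A reader might also infer that the model would steer IMT to the wrong patients. Step 4 shows that this rests on the assumed effect scale and response rates.

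**Conclusion.** The point holds as a mismatch between two Discussion statements and the design in the Methods. Study 4 can validate prediction of 8-week response in patients receiving IMT. No result from it, at any threshold, can separate benefit over nonindividualized therapy from good prognosis under either treatment. This follows from the single-arm design and needs no numerical assumption. The simulated figures are illustrations under assumed prognostic strength. The documents support neither a size nor a direction for the resulting error in patient selection. The correction is worth making because it changes what the program may conclude about choosing patients for IMT.

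**What to change.** 1. In Principal Findings and Future Directions, replace the benefit wording with: most likely to respond at 8 weeks while receiving IMT. This matches Study Design and Treatment-Response Prediction Model. Do not rest a treatment-selection or decision-support claim on study 4.

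2. Add an exploratory analysis in study 3, in the prediction-model analysis plan that is still to be finalized. Use out-of-fold model scores, fit treatment × score, and report the IMT-minus-nonindividualized response difference with 95% CI by score stratum. State in advance that it is hypothesis-generating for the definitive trial. The half-width of about 21 to 23 points exceeds the protocol's own 20-point threshold, so this analysis cannot license a decision-support claim either.

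The cost is two wording changes, one extra analysis of data already planned, and a more modest claim for study 4. No new patients or procedures are needed.

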### Comparison With Prior Work

Our program addresses 2 critical limitations in current music therapy practice: restricted accessibility and a “therapeutic ceiling” on efficacy. We adopted a receptive music therapy framework owing to its high feasibility and simplicity. This approach supports a scalable, clinic-to-home model where patients listen via headphones. To enhance therapeutic potency, we focus on the intervention’s core substrate: the musical stimulus itself. Unlike prior studies that selected from existing commercial libraries, our approach uses generative AI to create customized instrumental tracks. This allows for fine-grained tailoring based on granular participant preferences within a standardized therapeutic structure.

Neuroimaging research indicates that mental disorders are characterized by abnormalities in large-scale network connectivity, particularly within circuits governing affect, reward, and the default mode network [38,39]. Concurrent research demonstrates that music modulates these same networks [40]. For instance, preferred music enhances connectivity within the default mode network and alters coupling between the auditory cortex and the hippocampus, a region central to memory and emotion [41]. We hypothesize that targeted musical stimulation can ameliorate disorder-relevant dysfunction by modulating activity within these specific circuits. While functional overlap exists between brain regions implicated in psychiatric illness and those engaged by music, the therapeutic implications require targeted investigation. Consequently, this protocol adopts a neuroscience-guided approach that moves beyond simple preference-based personalization toward a biologically grounded model of IMT.

Neural activity monitoring via EEG serves as a primary tool for the development and refinement of IMT in this program. These techniques enable the observation of brain responses to musical stimulation and the delineation of biological response patterns. For example, preliminary evidence suggests that melody and rhythm may differentially engage language and motor cortices [42]. Correlating these biological markers with clinical outcomes provides an objective basis for the personalized selection of musical materials. Furthermore, real-time monitoring may eventually enable dynamic adjustment of treatment parameters based on brain-state changes. Consistent with this rationale, EEG is embedded throughout the program to track objective markers and to iteratively strengthen the neuroscientific basis of music therapy.

### Strengths and Limitations

This protocol has several strengths. First, the multistage design provides a structured translational pathway, progressing from mechanistic exploration through preliminary efficacy assessment to randomized comparison and predictive model validation. This sequential approach allows findings from each stage to inform the design and conduct of subsequent studies. Second, the integration of generative AI technology enables a degree of personalization that would be difficult to achieve through conventional music therapy practice, offering a scalable model that can be readily adapted across clinical settings. Third, the incorporation of neurophysiological monitoring alongside clinical outcome measures provides an opportunity to examine the biological mechanisms underlying treatment response, moving beyond purely symptom-based evaluation.

Several limitations should also be noted. First, the open-label design of study 2 precludes causal attribution of observed improvements to the intervention, as natural symptom fluctuation and regression to the mean cannot be excluded in the absence of a control group. However, this limitation is mitigated by the inclusion of a randomized controlled comparison in study 3. Second, complete participant blinding in the RCT is not feasible owing to the inherent differences between the 2 intervention arms, which may introduce differential expectancy effects; moreover, the weekly preference assessment in the IMT arm provides additional participant–researcher contact, engagement, and a sense of agency that is absent from the nonindividualized arm, so that any observed superiority of IMT could in principle reflect this added attention and engagement (a cointervention and attention effect) rather than personalization of the musical stimulus per se. To address these concerns, we have implemented several strategies to minimize bias, as described in the Randomization and Blinding section, including an attention-matched weekly questionnaire in the nonindividualized arm, baseline measurement of treatment credibility and expectancy with expectancy-adjusted sensitivity analyses, and a formal blinding-integrity (bang blinding index) assessment. We nonetheless recognize that these measures reduce, but cannot fully eliminate, the confounding of personalization with attention and expectancy; cleanly separating these components would require designs such as a 3-arm trial incorporating an attention-matched sham-personalization control, which we identify as an important direction for the definitive trial. Third, the pilot RCT is powered for precision of estimation rather than confirmatory hypothesis testing; consequently, the study may be underpowered to detect clinically meaningful differences within individual diagnostic subgroups, and subgroup analyses should be interpreted as exploratory. Because MDD, GAD, and PI differ in symptom profiles, neurobiology, and even in the affective trajectory of the intervention delivered, pooling them maximizes power for the overall comparison but cannot resolve whether the 3 disorders respond differently to IMT; we have therefore prespecified disorder-stratified estimation, a treatment × diagnosis interaction test, and a hierarchical Bayesian model that shrinks per-disorder estimates toward the pooled effect, and we explicitly refrain from drawing disorder-specific efficacy conclusions from this pilot. Definitive, disorder-specific inference will require an adequately powered, stratified trial. Fourth, all studies conclude at 8 weeks, and the durability of treatment effects beyond the intervention period remains unknown. Finally, although EEG offers excellent temporal resolution for capturing dynamic neural responses to music, it provides limited spatial resolution compared with functional MRI, which may constrain the ability to localize treatment-related changes in deep brain structures; in addition, the EEG analyses are exploratory and not powered for confirmatory neurophysiological inference, particularly at the level of individual disorders.

### Future Directions

If the pilot RCT demonstrates promising results, a fully powered, multicenter definitive trial will be warranted to confirm the efficacy of IMT across diverse clinical populations. To disentangle the personalization effect from the additional attention and engagement inherent in the IMT procedure, the definitive trial should consider a 3-arm design that adds an attention-matched sham-personalization control (in which participants complete weekly preference ratings but receive nonindividualized music), enabling the specific contribution of stimulus personalization to be isolated. Future studies should also incorporate longer follow-up periods (eg, 12 to 24 wk) to assess the durability of therapeutic effects and the potential for relapse prevention. Adequately powered, diagnosis-stratified samples will be required to draw firm disorder-specific conclusions for MDD, GAD, and PI, and to support confirmatory neurophysiological inference. The prediction model developed in study 4, if validated, could serve as a clinical decision-support tool for identifying patients most likely to benefit from individualized interventions; further refinement using machine-learning approaches with larger datasets would enhance its generalizability. Additionally, the integration of multimodal neuroimaging (combining EEG with fMRI or fNIRS) in future protocols could provide a more comprehensive understanding of the neural circuits engaged by IMT. Finally, investigating the applicability of the IMT framework to other psychiatric conditions, as well as to pediatric and geriatric populations, represents an important direction for extending the reach of this approach.

